## Methods

### Study Design

A longitudinal design will be performed in 15 single-case studies in which one case is a dyad of one unique client and one unique professional caregiver. More so than randomized controlled trials, multiple single case studies offer opportunities to study underlying processes and perform elaborate analyses on the individual and the environmental level [31]. In addition, people generally respond differently to stressful events and interpret different situations as stressful due to age, gender, experiences, and so on [32], underpinning the usefulness of single-case designs. The study will be performed in Dutch residential care organizations for people with ID. The organizations are part of a knowledge platform (in Dutch: “Kennisplatform EVB”) for sharing and developing knowledge regarding people with SPID and CB. This study was approved by the Faculty Ethics Committee of the Radboud University (NL-number: NL71683.091.19) February 12, 2020. Informed consent will be obtained from all caregivers and parent(s) or legal representative(s) of clients.

### Sample Size

This study included 15 dyads of a client and a professional caregiver. Due to the exploratory nature of the study, the sample size is not calculated. The sample size of 15 was determined based on feasibility due to the time investment necessary per case and the resources available to conduct this study. Single-case designs have additional sample size factors involved in determining power and accuracy besides the number of participants, including the number of observations [33]. In this study, we use several measurements for each dyad, increasing the power with a relatively small sample size.

### Eligibility

Clients will be eligible to enter the study if they meet the following inclusion criteria: (1) adults between 18 and 65 years of age, (2) anticipated to engage in CB regularly (ie, multiple times per week), (3) expected to reside in a designated institute for the upcoming 3 months, and (4) an IQ of 40 or below. Recruited caregivers (1) work a minimum of two days a week with the client and (2) are expected to work with the client for the upcoming 3 months. Clients for whom caregivers, behavioral experts, parents, or legal representatives expect to experience excessive distress from wearing the wearable, or will most likely damage the wearable, are excluded.

### Recruitment

Participants will be recruited during a symposium concerning clients with SPID and CB and through invitation letters among the 28 organizations that are part of the knowledge platform. First, the researcher informs interested caregivers about participation in the study via telephone or face-to-face discussions. Second, caregivers will indicate which client is eligible to participate in the study. Third, caregivers will contact clients’ parent(s) or legal representative(s) to inform them about the study with an information letter and request for consent to participate. Informed consent will be obtained from all caregivers and legal representative(s) of clients.

### Study Procedure

Clients and caregivers will wear the wearable during 20 sessions of 3 to 8 hours. The sessions do not interfere with daily routines and activities. The caregiver will attach the wearable to their own and their client’s wrist. Caregivers will follow a protocol developed specifically for clients with SPID and CB to attach the wearable to the client’s wrist because the attachment of the wearable may induce stress for both caregivers and clients due to the deviation from the daily routine [5] (see Multimedia Appendix 1). The protocol is personalized per dyad. To minimize the influence of the wearable on stress and behavior, clients and caregivers will wear the wearable prior to the study to familiarize themselves with it. When the wearable no longer induces stress to the client and the caregiver, we will start collecting measurements. The data are saved in the memory of the device and exported into a secured server via USB.

### Measures

#### Physiological Stress

Physiological measures of stress are obtained with the Empatica E4 wristband, a wearable wireless device that measures EDA, blood volume pulse (from which interbeat intervals and HR are derived), body temperature, and movements. This wearable provides advanced data quality compared to other available wearables, including artifact removal technique [34]. Validation studies show promising results [35,36].

HR is determined with a photoplethysmography (PPG) sensor, acquired at a 64 Hz sampling frequency. The amount of light through the skin reflected on the PPG sensor reflects the blood volume changes in the vessels with each heartbeat. HR (beats per minute) is derived from the blood volume pulse. EDA (microsiemens) is acquired at a 4 Hz sampling frequency using two electrodes through which a continuous current flows. When one’s sympathetic arousal level increases during stressful events, more sweat is produced, which increases EDA, whereas decreased sympathetic arousal results in a decrease in EDA. The extracted parameters are skin conductance level (SCL) and the number of peaks per minute (PPM). Measures of HR and EDA are corrected for temperature (degrees Celsius) and movement (measured with a 3-axis accelerometer) [34].

#### Challenging Behavior

For each incident that occurs during the sessions that the E4 wristband is worn, caregivers will report the following: date, time, type and severity of the incident, a description of the incident, whether the incident was expected (yes or no), and location. The incident registration form is based on the Modified Overt Aggression Scale [37]. The incidents are classified as either verbal aggression, aggression against property, auto aggression (ie, self-injury), or physical aggression. The severity of an incident is scored on a scale from 0 (light) to 4 (severe). Examples per type of incident are provided per severity score and personalized per client. Caregivers fill in the incident registration form on paper immediately after the incident has been averted.

#### Client Mood

Caregivers indicate the client’s mood every 15 minutes with green, yellow, orange, and red cubes. The definition of the colors is determined per client with caregivers and behavioral experts by associating each color to specific behaviors. Client mood scales will be based on a daily questionnaire reported in the electronic client record by some organizations. In addition, every organization makes use of a “signaling plan,” which includes 4 phases of behavior ranging from 0 (relaxed) to 4 (extremely stressed). The behaviors in these plans are translated into the 4 colors used to indicate mood in this study. To ensure feasibility, caregivers estimate the client’s mood throughout the day but only report the client’s mood on paper at the beginning of each shift and when the client’s mood changes.

#### Self-Reported Stress

Self-reported caregiver stress in the past month is measured prior to and after participation in the study. Caregivers fill in the 10-items Perceived Stress Scale (PSS-10) [38], which measures the degree to which situations are appraised as stressful on a 5-point Likert scale from 0 (never) to 4 (very often). A sum score between 0 and 40 gives an indication of perceived stress in the last month. Psychometric qualities are good [39]. The Dutch translation of the PSS-10 will be used.

In addition, self-reported caregiver stress in the 30 minutes prior to an incident of CB is measured on a scale from 1 (totally relaxed) to 10 (totally stressed out).

#### Demographics

The following client characteristics will be collected: sex, age, IQ, history of incidents, diagnoses, and medication. The following caregiver characteristics will be collected: sex, age, education, and work experience.

### Statistical Analyses

Descriptive statistics regarding incidents of CB and stress levels will be described in relation to demographic data. As measuring physiological stress in real-life situations results in artifacts (ie, disturbances in the signal due to excessive movements), the data will be visually inspected, and impossible values removed. Subsequently, data will be corrected automatically with a proven method described by Taylor and colleagues [40]. Statistical analyses will be performed in R-4.0.4.

EDA and HR of clients and caregivers in the 30 minutes prior to an incident of CB will be compared with 30 minutes of control periods in which the client did not engage in CB. A multilevel model with repeated measures (level 1) at the incident level (level 2) nested within the person level (level 3) will be used. For the repeated measures (level 1), the 30-minute sessions are divided into epochs of 5 minutes. Separate models for PPM, SCL, and HR will be considered. Covariates in the models include movement, temperature, and gender.

Recurrence Plots (RPs) of the 30 minutes prior to an incident of CB will be made. Cross-Recurrence Quantification Analysis (CRQA) will be performed to determine if patterns of stress in the time series of caregivers are recurring in the time series of clients, and vice versa, in a moment prior, simultaneously, or later in the time series [41]. The Recurrence Rate (RR), a ratio of the number of recurrent points over the total possible number of recurrent points, will be calculated. The RR indicates how often a point in one time series recurs in another time series. Determinism, which is the number of recurrent points that form a diagonal line in an RP relative to the total number of recurrent points, will be calculated. Determinism represents the recurrence of patterns over time, and a high determinism indicates the synchronization of patterns of physiological stress between the caregiver and the client. A diagonal Cross-Recurrence Profile provides insights into who is leading in the pattern of physiological stress prior to an incident. In other words, is the recurring pattern of stress first noticeable in a client and subsequently in the caregiver, or vice versa? CRQA is performed using the R package “crqa” [41].

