
### Our Study

The literature has shown the predictive value of physiological measures of stress for upcoming aggression in psychiatric patients and people with ASD. Although the possibilities of using wearables to study physiological stress in clients with SPID and CB have been shown, not much is known about patterns of physiological stress prior to CB in clients with SPID or in the caregivers that support them. Since the existing literature shows the well-being of caregivers is affected by stressors associated with clients’ CB, and the relationship with caregivers is important for clients to cope with stress and prevent CB, studying the reciprocity between clients’ and caregivers’ physiological stress is an eminent step in further increasing insights into patterns of stress and the origin of CB. Therefore, we hypothesize a reciprocal model in this study of stress and CB (Figure 1). The model suggests that: (1) client stress is associated with CB [2,15,17], (2) caregiver stress contributes to CB [4,7,14], (3) CB contributes to caregiver stress [6-9], and (4) caregiver stress impacts client stress and vice versa.

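### Control periods must be free of CB but the 30-minute pre-incident windows need not be, so if incidents cluster, arousal after one incident can count as the rise before the next

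*Protocol article*

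**What the plan says.** The Statistical Analyses section of the protocol article defines both sides of the main contrast. On the case side, "EDA and HR of clients and caregivers in the 30 minutes prior to an incident of CB will be compared". The comparator is "30 minutes of control periods in which the client did not engage in CB". The Objective, the research questions and the Conclusions likewise describe only the control or baseline side as free of CB.

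The structure of the data is given by "A multilevel model with repeated measures (level 1) at the incident level (level 2) nested within the person level (level 3) will be used", and "the 30-minute sessions are divided into epochs of 5 minutes", which makes six epochs per window. The covariates are movement, temperature and gender. The recurrence plots use the same 30 minutes.

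On recording, the Challenging Behavior section says: "For each incident that occurs during the sessions that the E4 wristband is worn, caregivers will report the following", with date and time among the items. Eligibility asks for clients "anticipated to engage in CB regularly (ie, multiple times per week" and sets no upper limit. Among the paths of the reciprocal model in Our Study is "3) CB contributes to caregiver stress".

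The article sets no minimum gap between incidents, no rule for merging close incidents, no bar on overlapping windows and no adjustment for time since the last incident.

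**The concern.** The two kinds of window are defined differently on the feature that matters most. A control window is excluded if CB occurs in it; a pre-incident window is not. When a second incident follows within 30 minutes, as in an escalation, its window holds the first incident and the recovery from it. The article's model expects CB to raise caregiver stress, and a further path lets caregiver and client stress act on each other. Such a window therefore mixes stress leading to CB with stress caused by CB.

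The error points the same way as the hypothesis, so it would be read as confirmation of research question 1. Two overlapping windows also enter shared minutes as if they were separate incidents. A joint reaction of client and caregiver to the earlier incident may appear in the recurrence plots as synchrony before CB.

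**Working it through.** The article states no alpha, power, effect size or incident rate, so there is no figure to reproduce. The arithmetic below only illustrates the size.

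**Inputs from the article.** 15 dyads; "Clients and caregivers will wear the wearable during 20 sessions of 3 to 8 hours", that is 60 to 160 h per dyad (110 h at the 5.5 h midpoint); 30-minute windows.

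**Assumed inputs.** 112 waking hours per week. Post-incident arousal of +1 within-person SD, halving every 15 minutes. Exponential gaps within a bout with mean 10 minutes. Geometric bout size with mean m. Bout rate 0.03 to 0.1 per hour, which is 0.03 × 112 = 3.4 to 0.1 × 112 = 11.2 bouts per week. No true rise before CB.

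**Step 1: incidents spread evenly.** P(an earlier incident within 30 min) = 1 − exp(−0.5 × hourly rate). At 3, 7, 14 and 28 incidents per week this is 1.3%, 3.1%, 6.1% and 11.8%.

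**Step 2: incidents in bouts.** The share of incidents that are not first in a bout is 1 − 1/m, and P(gap < 30) = 1 − exp(−30/10) = 0.950.
- m = 1.5: 0.333 × 0.950 = 32%.
- m = 2: 0.500 × 0.950 = 48%.

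Simulated shares at 3 to 14 incidents per week are 33 to 35% and 48 to 50%. They are slightly higher because separate bouts can also overlap.

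**Step 3: elevation of the window mean.** With k = ln 2/15 = 0.0462 per minute, an earlier incident x minutes before the index incident raises the 30-minute mean by (1 − 2^(−x/15))/(30k), where 30k = 1.386. At x = 10 this is (1 − 0.630)/1.386 = 0.27 SD. Averaged over gaps below 30 minutes, the mean of 2^(−x/15) is [0.1/0.1462] × (1 − exp(−4.386))/0.950 = 0.711, so the elevation is (1 − 0.711)/1.386 = 0.21 SD. Times the shares in step 2, that is 0.21 × 0.32 = 0.07 SD and 0.21 × 0.48 = 0.10 SD. This counts only the nearest earlier incident. The same formula with half-lives of 5 to 20 minutes and mean gaps of 10 to 20 minutes gives 0.04 to 0.10 SD at 33% contaminated and 0.07 to 0.14 SD at 50%.

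**Step 4: simulated studies.** 15 clients, 20 sessions of 5.5 h, 5-minute autocorrelation 0.8, window means compared within client, t-test over clients. A false rise is a significant positive result (nominal 2.5%).

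| Setting | 1.5 per bout | 2 per bout |
|---|---|---|
| Mean gap about 10 min, 0.03 to 0.1 bouts/h | +0.07 to +0.14 SD; 8 to 35% | +0.17 to +0.30 SD; 21 to 92% |
| Mean gap 10 min, 0.1 bouts/h, responses from non-additive to additive | +0.11 to +0.15 SD; 31 to 40% | +0.20 to +0.28 SD; 63 to 83% |
| Mean gaps 5 to 15 min, 0.1 bouts/h, non-stacking responses | +0.08 to +0.12 SD; 13 to 29% | +0.14 to +0.18 SD; 35 to 61% |
| As the row above, 0.03 bouts/h | +0.05 to +0.08 SD; 6 to 9% | 11 to 17% |

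Without clustering at 0.1 bouts/h, 5% of windows are contaminated, the false difference is about +0.01 SD and false rises occur in 3 to 4%. Keeping only incidents with 30 CB-free minutes before them gives about 0 to +0.02 SD and 1 to 5%.

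**Step 5: slope within the window.** Split the window into two halves of 15 minutes (15k = 0.693). An earlier incident 25 minutes before the index gives (1 − 0.630)/0.693 = 0.53 SD in the first half and (0.630 − 0.315)/0.693 = 0.45 SD in the second, a slight fall. One 10 minutes before gives 0 and 0.53 SD, a clear rise. A slope test is therefore less affected when the earlier incident lies early in the window, but not when gaps are short.

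**The case against.** The strongest objection is that the article does not say that each logged incident opens its own window. It says that each is recorded, and it speaks of the time before an incident. Turning records into index incidents is a detail that a full protocol or analysis plan may settle. A reader might infer that the authors decided to admit contaminated windows; the text shows silence, not a decision. What remains is that the article itself fixes both window definitions and attaches the CB-free condition to one of them only.

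Second, an incident may already mean a whole episode. The form is completed once the incident has been averted, and it carries a description and one severity score. A bout of self-injury could then yield one form and one window. That is possible, and it is why the point is conditional.

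Third, the simulations are not the planned analysis. They reduce each window to a mean, omit the movement and temperature covariates, and use a t-test in place of the three-level model. They show direction and rough size, not the error rate of the planned model.

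Fourth, controls drawn soon after CB could offset the bias. They do so only partly: in the second row of the table, controls had to be CB-free but needed no distance from earlier CB, and the bias remained.

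Finally, the study is declared exploratory. It nevertheless hypothesises a significant rise. The limitation about unassessed causes of stress does not cover earlier incidents, whose times are recorded.

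**Conclusion.** The point holds in conditional form. As written, the definitions let post-incident arousal count as pre-incident arousal whenever incidents fall within 30 minutes of each other, and the bias favours the hypothesis. Its size cannot be known from the article, which gives no clustering data. Under the assumptions listed, it runs from negligible without clustering, through +0.07 to +0.14 SD at 1.5 incidents per bout, to +0.17 to +0.30 SD at 2 per bout. The 92% at the top of the last range is the highest value obtained; other settings at the same bout rate gave 35 to 83%.

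Two stronger readings are not supported. A reader might infer that the main contrast is bound to give a false positive, but that requires frequent clustering, which is undocumented. A reader might also infer that standard errors are demonstrably too narrow and synchrony demonstrably inflated. Both follow plausibly from shared minutes and shared incidents, but neither was computed. The response to CB is also stated directly for caregivers only; for clients it is a further assumption. This is a cheap improvement, conditional on clustering, and not an established flaw in the result.

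**What to change.** In the multilevel models and the cross-recurrence analysis, use as index incidents only those with at least 30 CB-free minutes before them in the same session, with 60 minutes as a sensitivity analysis. Require the same minimum distance from earlier CB for control periods, measured to the same point of the window, so that neither side sits systematically closer to earlier CB. Let no epoch enter twice. Describe the remaining clustered incidents and include them in a sensitivity analysis. It would also help to state whether one form covers an act or a whole episode.

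The rule needs a few sentences and a filter on times already recorded; data collection does not change. The cost is fewer pre-incident windows, and a main contrast that then applies to the first incident of a bout, although later incidents may have a build-up of their own. The 60-minute version also drops some windows with no CB in them. If incidents rarely cluster, almost nothing is lost.

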**Figure 1 figure1:**
[figure not shown]
A reciprocal model of stress and challenging behavior in caregivers and people with severe to profound intellectual disability.

This naturalistic study explores patterns of physiological stress (ie, EDA and HR) in clients with SPID and professional caregivers prior to CB in Dutch residential institutes and the synchronization between client and caregiver patterns of stress. We address the following research questions:

Do patterns of physiological stress in clients with SPID and professional caregivers in the 30 minutes preceding an incident of CB differ from control periods of 30 minutes without CB?Do the physiological stress levels of caregivers impact clients’ physiological stress levels and vice versa?

We hypothesize that a significant rise in EDA and HR is apparent in both clients and caregivers in the 30 minutes preceding an incident of CB compared to baseline levels when the client does not engage in CB. In addition, we hypothesize physiological synchrony—a mutual change in autonomic nervous system activity—between caregivers and people with SPID and CB. Physiological synchrony has been shown in some interaction partners, including parent-infant dyads [27,28], strangers [29], and romantic couples [30]. However, to our knowledge, physiological synchronization has not been studied before in dyads of professional caregivers and clients with SPID and CB.

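### High determinism before incidents is read as caregiver–client synchrony without a chance or control reference, although determinism barely responds to coupling

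*Protocol article*

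**What the plan says.** All of this stands in the protocol article, mostly under Statistical Analyses.

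- Windows: "Recurrence Plots (RPs) of the 30 minutes prior to an incident of CB will be made".
- Determinism is defined as "the number of recurrent points that form a diagonal line in an RP relative to the total number of recurrent points", and its reading is given: "a high determinism indicates the synchronization of patterns of physiological stress between the caregiver and the client".
- Leading: "A diagonal Cross-Recurrence Profile provides insights into who is leading in the pattern of physiological stress prior to an incident".
- Control periods appear in the same section for the multilevel models, where EDA and HR before incidents "will be compared with 30 minutes of control periods in which the client did not engage in CB". They are not mentioned for CRQA.
- The question that CRQA serves (Our Study) is general and not tied to the run-up to an incident: "Do the physiological stress levels of caregivers impact clients’ physiological stress levels and vice versa". The same section hypothesizes physiological synchrony between caregiver and client.

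No cut-off for a high value, no surrogate or mismatched pairs, and no radius, embedding or minimum line length are given.

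**The concern.** The article does more than leave settings open: it says what a high value means. That reading is valid only if determinism rises when two people's signals are coupled and stays low when they are not. Determinism counts how much of the recurrence falls on diagonal lines anywhere in the plot. Two signals that each change slowly form such lines whenever they pass through similar values, whether or not they are related. Skin conductance level is such a signal, and EDA is sampled at 4 Hz.

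The diagonal profile has a similar weakness. It has a maximum at some lag for any pair, so one profile's peak is not evidence of a leader until it is set against what unrelated pairs produce.

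CRQA is the only analysis described for the second research question. If its main index does not respond to coupling, the study cannot answer that question in either direction.

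**Working it through.** **Inputs from the article.** Window of 30 minutes before an incident; the definition and reading of determinism quoted above; EDA at 4 Hz (Physiological Stress), so 30 × 60 × 4 = 7,200 samples per window. The article states no CRQA figure, so there is nothing to reproduce.

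**Assumed, because the article gives no settings.** Two standardized series of 900 points (1,800 s at one point per 2 s), no embedding, radius set so that 5% of points recur, minimum line 2, and 15 simulated pairs per setting, unless noted. Signals are white noise, AR(1) with coefficient φ, or noise low-passed twice with time constant τ in points. Coupling is a simultaneous linear correlation ρ.

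**Formulas.** R(i,j) = 1 if |x_i − y_j| ≤ radius, otherwise 0. Recurrence rate RR = ΣR / N². Determinism DET = (recurrent points on diagonal lines of at least the minimum length) / ΣR. Diagonal profile at lag k = mean of R(i, i+k) over i.

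**Step 1: effect of smoothness, unrelated pairs (ρ = 0).** Mean DET is 0.098 for white noise, 0.211 at φ 0.9, 0.403 at φ 0.98 and 0.599 at φ 0.995.

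**Step 2: effect of coupling, smoothness held fixed.**

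| Setting | DET, ρ 0 | DET, ρ 0.5 | DET, ρ 0.8 |
|---|---|---|---|
| AR(1), φ 0.98 | 0.403 | 0.403 | 0.432 |
| range over pairs | 0.345–0.507 | 0.304–0.480 | 0.333–0.554 |
| Low-passed, τ 10 | 0.646 | 0.654 | 0.641 |
| Low-passed, τ 30 | 0.974 | 0.971 | 0.976 |
| Low-passed, τ 60 | 0.998 | 0.997 | 0.998 |
| AR(1), φ 0.98, radius 0.3 SD (separate run, 30 pairs) | 0.84 | 0.83 | 0.84 |
| AR(1), φ 0.98, minimum line 5 | 0.010 | 0.011 | 0.012 |

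Going from white noise to φ 0.995 with no coupling moves DET by 0.599 − 0.098 = 0.501. Going from no coupling to ρ 0.8 at φ 0.98 moves it by 0.432 − 0.403 = 0.029, with overlapping ranges.

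**Step 3: effect of the settings.** For unrelated pairs at φ 0.98 and radius 0.3 SD, another run gave DET of 0.81 at minimum line 2, 0.30 at 5 and 0.04 at 10. Whether a value looks high depends on a choice that the article does not state.

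**Step 4: an index that does respond.** Mean recurrence in the diagonal profile within ±10 lags (φ 0.98, 60 pairs per setting):

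| ρ | Mean | 5th–95th percentile |
|---|---|---|
| 0 | 0.051 | 0.035–0.071 |
| 0.5 | 0.070 | 0.049–0.093 |
| 0.8 | 0.097 | 0.073–0.132 |

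The 95th percentile of unrelated pairs, 0.071, serves as a cut-off here. At ρ 0.8 the 5th percentile (0.073) lies above it. At ρ 0.5 the mean (0.070) lies just below it, so one window is often not enough and a dyad's incidents need to be combined.

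**Step 5: the leader.** In pairs coupled at ρ 0.8 with no lag, the profile peaked exactly at lag 0 in 20–92% of pairs, depending on the settings. So 100 − 92 = 8% to 100 − 20 = 80% of pairs without any leader peaked away from zero. In uncoupled pairs the sign of the peak was about even (46–51% positive).

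**The case against.** The strongest case on the other side has five parts.

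- **A condensed article.** Radius, line length and a surrogate procedure may stand in a full protocol or analysis plan that is not shown. That is fair, and their absence is not the point here. The point is the interpretive sentence, which is stated and calls for no reference.
- **No decision rule.** A reader might infer that every dyad would be declared synchronized and that the hypothesis could never be refuted. The text does not support this: it sets no cut-off, and with long minimum lines unrelated pairs score near zero. What stands is that determinism hardly differs between coupled and unrelated pairs under the short and moderate line lengths tested.
- **Control windows are not excluded.** A reader might infer that CRQA is expressly confined to pre-incident time. The plots and the leading profile are tied to it, but the sentences on recurrence rate and determinism name no window. The accurate statement is that no other window is described.
- **False leaders.** In simulation, 97% or more of uncoupled profiles peak away from lag 0. It is tempting to call this the rate of false leaders. It is not, since truly coupled pairs also often peak off zero, and in uncoupled pairs the sign would balance out over incidents. What stands is that a single peak needs a null.
- **Movement and shared rises.** A reader might infer that CRQA is run on uncorrected signals. Physiological Stress says that HR and EDA are corrected for movement and temperature, whereas Statistical Analyses and the Discussion place this in the models; that is an ambiguity. Nor is a common pre-incident rise clearly a fault. The article expects "a significant rise in EDA and HR is apparent in both clients and caregivers in the 30 minutes preceding an incident of CB" and defines synchrony as mutual change. The simulated effect of a shared rise is also uneven: near-diagonal recurrence relative to overall was 1.03, 1.14 and 1.32 for rises of 1, 2 and 3 SD in one setting, and a 2-SD rise moved it only from 0.052 to 0.053 in smoother series.

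The exploratory label limits how much weight the result carries. It does not make an index informative when it does not respond to coupling.

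**Conclusion.** The point holds as a wrong stated reading. For autocorrelated signals, whole-plot determinism mainly measures smoothness and settings. Coupling up to ρ 0.8 changed its mean by at most 0.029 in the settings tabulated, against 0.501 from smoothness alone. High determinism therefore cannot support the synchrony hypothesis, and low determinism cannot refute it. A single profile's peak lag cannot show who leads without a null. With no control-window CRQA described, nothing could be said about whether any synchrony is particular to the run-up to an incident.

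This rests on simulated AR(1) and low-passed signals, simultaneous linear coupling, no embedding and assumed settings. Absolute values will differ in real E4 data. The finding carried forward is the lack of separation, not any particular level of determinism.

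**What to change.** 1. Base the synchrony claim on one pre-chosen index: recurrence near the main diagonal of the diagonal cross-recurrence profile. Base the leading claim on profile asymmetry combined over a dyad's incidents. Compare each with surrogate pairs made from the client's series in one session and the same caregiver's series in another, at the same position before an incident. With k usable sessions there are k(k − 1) such pairs: 20 at k = 5, 90 at k = 10 and 380 at k = 20 (k is assumed, since incident counts are unknown). They are not independent, and few incidents give a rough reference.
2. Run the same CRQA, with the same settings, in the dyad's control windows. Compare pre-incident with control within dyad, each relative to its own surrogates. Surrogates show whether synchrony exceeds chance; control windows show whether it is specific to the time before incidents.
3. Report determinism and recurrence rate as descriptive. A surrogate band on determinism would have little power, and accepting any one of several indices would add multiplicity. Replace the interpretive sentence, for example with: *Synchrony will be inferred when near-diagonal recurrence exceeds that of surrogate pairs; determinism and recurrence rate are descriptive.*
4. State whether the movement and temperature correction is applied to the series that enter CRQA.

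The cost is wording and some extra analysis on data that the study collects anyway. The downside is that some dyads will no longer be called synchronized.
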